### Blinding

2.10

This is an open-label trial; therefore, neither the patients nor the practitioners will be blinded to the entire process. However, other researchers, including outcome assessors and statisticians, will be blinded to eliminate potential bias. Assessors, who are not involved in randomization or acupuncture performance, will ask simple and necessary questions to participnats for outcome assessments so that they cannot assume the groups of each participant.

### Data collection methods and management

2.11

All research assistants, including the CRCs at the 3 centers, will be trained using a standard operating procedure to promote data quality. The laboratory data will be analyzed in the medical laboratories of South Korea and China that meet the international standard ISO 15189^[^28^,^^29^^]^ to reduce errors between each center.

Data collection procedures will be conducted in compliance with the approved protocol and the standard operating procedure of the trial to ensure good data quality. All data, including the CRF and worksheet, will be kept in a cabinet with locking devices. At the end of the trial, all data written in the CRF will be coded in separate computer files. Data entry will be performed using a double-input method, and the matching work will be conducted after reviewing inconsistent data. When the data are matched, a data clarification form will be completed and validated, and the resolution will be reflected in the data. Computer files in computer storage devices will be kept confidential under password protection during and after the trial.

### Data and safety monitoring

2.12

A quality monitoring committee will be established independent of the researchers and sponsors. All data will be verified to ensure that they are recorded and reported accurately and completely and are consistent with the original data. The principal investigator will be responsible for monitoring the entire process. The entire study process will be under strict supervision. All adverse events and other unintended effects of acupuncture or trial conduct will be collected by the CRC. The principal investigators at each trial site, who will be notified by the CRC, will assess whether the adverse events are relevant to acupuncture and whether the trial should be amended or ended.

### Statistical methods

2.13

All statistical analyses will be performed using SAS version 9.4 (SAS Institute. Inc., Cary, NC) with a two-tailed test. The level of significance will be set at 5%. Missing data will be substituted using multiple imputations.

The analysis set will consists of a full analysis set (FAS), per-protocol (PP) set, and safety set. The main analyses will be conducted using FAS. A FAS is described as set that is as complete and close as possible to the intention-to-treat. The efficacy test will be assessed by FAS analysis and PP analysis. The safety test will be assessed by intent-to-treat analysis, as well as by PP analysis.

Baseline characteristics of the groups with continuous data will be compared using an independent *t*-test or a Wilcoxon rank-sum test. Baseline characteristics with categorical data will be compared using a Chi-Squared test or Fisher exact test.

The primary outcome measure in this study will be the mean change in menstrual frequency from baseline to 16 and 32 weeks after the start of the trial. To analyze menstrual frequency as the primary outcome, we will perform an analysis of covariance considering the baseline menstrual frequency as the covariate and treatment group as the fixed factor. Additionally, intra-group menstrual frequency changes from baseline to post-treatment will be analyzed using a paired *t*-test or Wilcoxon signed-rank test.

The methods used to analyze the secondary outcome measures will be the same as those used for the primary outcome analyses. If the data type is categorical, it will be analyzed using a Chi-Squared test or Fisher exact test.

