### Study design and setting

2.1

This multi-country, multi-center, assessor-blinded RCT will be performed at the following three hospitals: Acupuncture and Moxibustion Hospital of China Academy of Chinese Medical Sciences (CACMS; Beijing, China), Dongzhimen Hospital (Beijing, China), and Kyung Hee University Hospital at Gangdong (Seoul, Republic of Korea). The study period will be 32 weeks, including 16 weeks of intervention and 16 weeks of follow-up. The study plan is summarized in Figure 1. This study protocol followed the Standard Protocol Items: Recommendations for Interventional Trials guidelines (SPIRIT).

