### Sample size

2.8

We calculated the sample size based on a previous study that used the same variables as ours as the primary outcome.^[12]^ For the current study, the mean difference and standard deviation are assumed as 0.14 and 0.17, respectively, between the acupuncture and control groups. In other words, the effect size for menstrual frequency is assumed to be approximately 0.8. In our study, participants will be randomized into 2 groups in a 1:1 ratio after considering 5% of the significance level (α) and 80% of the power (1−β). Therefore, the present study will include 50 participants in total, divided into 2 groups of 25. Considering a dropout rate of 15%, at least 60 participants are required.

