### Randomization and allocation concealment

2.9

In this trial, participants will be randomly assigned to either the acupuncture group or control group in a 1:1 ratio using a table of random numbers. An independent, blinded statistician will generate random numbers using the block randomization method of SAS version 9.4 (SAS Institute. Inc., Cary, NC) with a block size of 4. The investigator will be subsequently notified of the number assigned to each participant, and the participants will be given a random number on their second visit. The allocation table of participants will be kept by an independent statistician until the end of the study. The clinical research coordinator (CRC) will enroll the participants, generate the allocation sequence, and assign participants to the intervention groups.

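### The ANCOVA has no hospital term in a three-hospital, two-country trial; adding it costs 2 degrees of freedom and recovers precision

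*Protocol article*

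**What the plan says.** Study design and setting (2.1): "This multi-country, multi-center, assessor-blinded RCT will be performed at the following three hospitals". Two are in Beijing and one is in Seoul.

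Randomization and allocation concealment (2.9): allocation is 1:1 by block randomisation "with a block size of 4". The section does not say whether the blocks are kept within hospitals.

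Data collection methods and management (2.11): "The laboratory data will be analyzed in the medical laboratories of South Korea and China". These laboratories are accredited to ISO 15189, and staff at the three centres follow a common standard operating procedure.

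Statistical methods (2.13): for menstrual frequency, "we will perform an analysis of covariance considering the baseline menstrual frequency as the covariate and treatment group as the fixed factor". Secondary outcomes are analysed the same way, except that categorical ones go to a Chi-squared or Fisher test. Tests are run "with a two-tailed test" at 5%.

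Sample size (2.8): "the mean difference and standard deviation are assumed as 0.14 and 0.17, respectively", giving 25 women per arm for 80% power and 60 in total after 15% dropout.

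**The concern.** The article does not leave the model open. It names one covariate and one factor, and hospital is neither. Hospitals can differ in case mix, in how acupuncture and lifestyle advice are delivered and, for the hormone outcomes, in the assay. Any such difference stays in the residual variance of the stated model.

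The consequence depends on how the allocation list is organised, which the article does not say.

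- **One list across hospitals:** arm sizes within a hospital are left to chance. The model cannot correct an imbalance, and between-hospital variance counts as noise.
- **One list per hospital:** the design removes between-hospital variance from the treatment comparison, but the model still charges for it in the standard error.

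At stake are the precision of the primary and secondary estimates and, in the second case, a test that runs below its nominal level. The trial is a pilot meant to inform a full-scale trial, so its effect and variance estimates are likely to be reused.

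**Working it through.** **1. The plan's own figure.** Inputs from Sample size (2.8): difference 0.14, SD 0.17, α = 5% two-sided, power 80%.

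- Effect size = 0.14/0.17 = 0.824; the plan states that "the effect size for menstrual frequency is assumed to be approximately 0.8".
- n per arm = 2 × (1.96 + 0.8416)² / 0.8² = 24.5, so 25. With 0.824 it is 23.1, so 24.
- Dropout: 25/0.85 = 29.4, so 30 per arm and 60 in total.

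The stated sample size reproduces and is not in question.

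**2. Assumptions not in the documents.** The share ρ of outcome variance due to hospital is taken as 5% to 30%. Hospitals are taken as equal in size: 20 women each of 60 randomised, or 16 each of 48 evaluable. The 48 is used because it divides into three hospitals with whole blocks of 4; the plan's evaluable number is 50.

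**3. One list across hospitals.** In simulated lists of 15 blocks of 4 over three hospitals of 20, at least one hospital splits 13:7 or worse in about 35% of trials, and 14:6 or worse in about 13%.

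Effect of one 13:7 split if that hospital's mean differs by an assumed 0.5 SD:

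- Difference between arms in the proportion from that hospital = 13/30 − 7/30 = 0.20.
- Shift = 0.20 × 0.5 = 0.10 SD = 0.10 × 0.17 = 0.017 cycles/month.
- 0.017/0.14 = 12% of the assumed effect.

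The shift can go either way and averages to zero over randomisations. In simulation (60 women, baseline correlation 0.5, ρ from 0 to 0.20) the model without hospital had type I error of 5.0% to 5.3%.

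**4. One list per hospital.** With total variance 1, the true variance of the treatment difference is about 4(1 − ρ)/N, while the model without hospital estimates about 4/N. The standard error is therefore too large by a factor 1/√(1 − ρ), and the type I error is about 2 × [1 − Φ(1.96/√(1 − ρ))].

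| ρ | SE factor | Type I error, formula | Simulated, 48 women | Simulated, 60 women |
|---|---|---|---|---|
| 5% | 1.03 | 4.4% | – | 4.4% |
| 10% | 1.05 | 3.9% | 3.5% | 3.4% |
| 20% | 1.12 | 2.8% | 2.8% | 2.3% |
| 30% | 1.20 | 1.9% | 2.4% | – |

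With hospital in the model the simulated type I error is about 5%. In the 60-woman runs, where the baseline covariate removes part of the residual variance, the standard error was too large by 2%, 6% and 16% at ρ = 5%, 10% and 20%.

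**5. Power at the design effect, 48 evaluable.** The signal is 0.824 × √(48/4) = 2.853. The critical value is 2.014 without hospital (45 df) and 2.017 with it (43 df).

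- Per-hospital lists, without hospital: Φ((2.853 − 2.014)/√(1 − ρ)).
- Per-hospital lists, with hospital: Φ(2.853/√(1 − ρ) − 2.017).
- One list, without hospital: Φ(2.853 − 2.014).
- One list, with hospital: as the second line, with 2.853 divided by √(1 + 2/45) for the average loss from arm-by-hospital imbalance.

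| ρ | Per-hospital lists, without → with | One list, without → with |
|---|---|---|
| 5% | 81% → 82% | 80% → 80% |
| 10% | 81% → 84% | 80% → 82% |
| 20% | 83% → 88% | 80% → 87% |
| 30% | 84% → 92% | 80% → 91% |

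Simulation with 48 women at ρ = 10%, 20% and 30% gave 79 → 82, 81 → 87 and 82 → 91 for per-hospital lists, and 80 → 82, 78 → 85 and 79 → 89 for one list. Formula and simulation agree on the size of the gain.

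**The case against.** A reader might infer that the treatment effect is confounded with hospital, or that the test is invalid. The documents do not support either. With one list, imbalance arises by chance, the estimate is unbiased on average and the standard error already allows for it. The 35% and 13% figures describe arm splits, not wrong results. With lists by hospital the error is in the conservative direction, so no extra false positives arise.

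A reader might also infer that randomisation is not stratified. The article gives the method and block size but no strata. That is silence in a condensed article, and the full protocol may name them. If it does, the stated ANCOVA still omits a design factor.

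Further points that stand:

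- The hospital share is assumed. At 5% almost nothing is gained.
- Power without hospital stays at or close to the 80% target, so the plan's own goal is not broken.
- Laboratory differences do not affect menstrual frequency. For hormones, adjusting for each woman's baseline absorbs part of a constant laboratory offset, and accreditation, common procedures and a fixed acupuncture protocol should reduce differences between centres.
- If acupuncture works differently by practitioner or country, that is a treatment-by-hospital effect, which a main-effect term does not address.

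None of this is a reason to leave hospital out of a model that is already written down term by term, when including it is almost free.

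**Conclusion.** The point holds as one of precision and, if lists are by hospital, of matching analysis to design. The stated ANCOVA should include hospital. Omitting it causes no bias on average and no inflated type I error.

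The cost of omission is about 0–1 points of power at a 5% hospital share, about 3 at 10% and about 5–11 at 20–30%. With per-hospital lists, type I error is also below nominal: about 2–3% over most of the 10–30% range (3.4–3.9% at 10%) and 4.4% at 5%.

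These sizes rest on the assumed hospital share, equal hospitals, 48 evaluable women and the plan's effect of 0.14/0.17. The direction does not depend on the exact share, though at the lowest share the gain is negligible. The change is worth making, but the planned result would not be invalid without it.

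**What to change.** Before unblinding, restate the model in Statistical methods (2.13), for menstrual frequency and every continuous secondary outcome, as:

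change = the outcome's own baseline value + treatment group + hospital (3 levels, fixed effect).

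In Randomization and allocation concealment (2.9), state whether the blocks of 4 are kept separately for each hospital. This is a clarification, not the correction of an error shown by the article.

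The cost is 2 degrees of freedom and a line of text. The sample size stays at 60.

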#### Inclusion criteria

2.3.1

The inclusion criteria are as follows:

1.oligomenorrhea (menstrual cycle >35 days or <8 cycles per year) with at least one of the following 2 criteria:A.Hyperandrogenism (clinical, biochemical, or both);B.Polycystic ovarian morphologic features (≥12 antral follicles of 2–9 mm diameter in either ovary; an ovarian volume **≥**10 mL in either ovary; or both);2.Age 20 to 40 years;3.Voluntary agreement to participation in the trial and provide informed consent prior to treatment.

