#### Primary outcome

2.5.1

The primary outcome is the mean change in menstrual frequency (menstrual cycle/month) from baseline to 16 weeks and 32 weeks (follow-up) after the start of the trial. The menstrual frequency will be assessed to evaluate the improvement in ovulatory functions and restoration of menstruation of PCOS patients.^[19]^ The average menstrual frequency for the last year will be recorded as the baseline evaluation. The average menstrual frequency for 16 weeks during the treatment period will be recorded at a close-out evaluation, and that for another 16 weeks during the follow-up period will be recorded at a follow-up evaluation.

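### The added within-arm paired tests of change from baseline cannot show an acupuncture effect and should become description only

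*Protocol article*

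**What the plan says.** The hypothesis in the Introduction is comparative: acupuncture is expected to do better than usual care. Section 2.13 of the protocol article analyses menstrual frequency by ANCOVA, with baseline frequency as covariate and group as factor. It then adds that "intra-group menstrual frequency changes from baseline to post-treatment will be analyzed using a paired" t-test or Wilcoxon signed-rank test. The secondary outcomes are to be analysed by the same methods, so the within-arm tests extend to every continuous secondary outcome. Testing is at 5%, "with a two-tailed test". Nothing in the article limits how the within-arm p-values may be read.

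Four other statements bear on what those tests measure:

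- Section 2.5.1, baseline: "The average menstrual frequency for the last year will be recorded as the baseline evaluation".
- Section 2.5.1, later values: averages over the 16-week treatment period and over a further 16 weeks of follow-up.
- Section 2.3.1, entry on oligomenorrhea: "menstrual cycle >35 days or <8 cycles per year". Section 2.3.2 excludes cycles of more than 3 months.
- Section 2.4: the acupuncture arm is also advised to follow the usual-care regimen that the control arm receives.

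**The concern.** A paired test asks whether the mean change in one arm is zero. That null can be false with no acupuncture effect at all. Women enter because their past frequency is low, so later values tend to rise. Baseline and outcome are averaged over windows of different length and coarseness. Lifestyle advice may move both arms.

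The time-window argument is specific to menstrual frequency. For the other outcomes the general objection remains: the test has no comparator. Entry can also depend on hyperandrogenism, follicle count or ovarian volume, so regression to the mean can reach testosterone and the ultrasound measures too.

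What is at stake is interpretation. In a small pilot meant to inform a full-scale trial and guidelines, a significant change with acupuncture beside a non-significant one with control could be read as efficacy when the arms do not differ.

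**Working it through.** **The plan's own figure.** Section 2.8 states that "the mean difference and standard deviation are assumed as 0.14 and 0.17, respectively", that "the effect size for menstrual frequency is assumed to be approximately 0.8", with two-sided 5% and 80% power.

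- n per arm = 2(1.960 + 0.842)²/d². With d = 0.8 this is 15.7/0.64 = 24.5, rounded up to 25. With d = 0.14/0.17 = 0.824 it is 24.
- Dropout: 25/0.85 = 29.4, rounded up to 30 per arm, 60 in total. The stated sample size reproduces, and this point does not change it.

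**Resolution of the two windows.** 16 weeks is 112/30.4375 = 3.68 months. One period moves the outcome by 1/3.68 = 0.27 cycles/month and the one-year baseline by 1/12 = 0.083.

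**Drift with no effect of any kind.** The article gives no cycle distribution, so these inputs are assumptions: woman-specific mean cycle lognormal with median 40 to 50 days and log-SD 0.25 to 0.30; within-woman CV 0.25 to 0.40. Baseline is menses in 365 days divided by 12; outcome is menses in 112 days divided by 3.68; n is 25 or 30 per arm.

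- Stated entry rule (over 35 days, read as the last-year mean, or fewer than 8 cycles/year; cycles over 3 months excluded): mean drift about 0.00 to 0.03/month, paired t-test rejects in about 4% to 9% of arms against a nominal 5%.
- Most women entering with fewer than 8 cycles/year: rejection in about 6% to 43%.

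The ends of these ranges are approximate and move by some percentage points with how the exclusion is coded and with simulation error. A repeat of the model gave the same picture, with somewhat higher upper ends.

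A separate simulation, restricted to fewer than 8 cycles/year, used medians of 40 to 55 days and in some settings added year-to-year variation and error in the recorded baseline. False improvement ran from 4% to 79% at n = 30, against 2.5% in that direction. The between-arm ANCOVA rejected in 3.2% to 5.6% of null trials, close to the nominal 5%.

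**Equal change b in both arms.** Take the SD of change as 0.17 (an assumption; section 2.8 gives it for the between-group calculation). The chance p of a significant rise in one arm comes from the noncentral t with noncentrality b√n/0.17. Acupuncture significant and control not then has probability p(1 − p).

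| b (cycles/month) | n | b√n/0.17 | p | p(1 − p) |
|---|---|---|---|---|
| 0.03 | 25 | 0.88 | 0.133 | 0.115 |
| 0.03 | 30 | 0.97 | 0.153 | 0.130 |
| 0.05 | 25 | 1.47 | 0.292 | 0.207 |
| 0.05 | 30 | 1.61 | 0.344 | 0.226 |
| 0.07 | 25 | 2.06 | 0.506 | 0.250 |
| 0.07 | 30 | 2.26 | 0.587 | 0.242 |

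That is about 12% to 25% of trials. With no drift it is 0.025 × 0.975 = 2.4%. The largest b shown is half the design difference of 0.14.

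**The case against.** The strongest reply is that the plan does not rest efficacy on these tests. The hypothesis and sample size are between-arm, the ANCOVA comes first, and the paired tests are introduced as an addition. A full protocol or SAP, not shown, may say how to read them. This stands, and it limits the harm to misreading. It does not make the tests informative about the trial's question, and the article does specify them.

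Four stronger readings are tempting, and the document does not support them:

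- *The primary analysis is biased.* Baseline is defined identically in both randomised arms, and the ANCOVA held its level.
- *Large false-positive inflation is established.* The entry rule is either/or, so a woman with 36-day cycles (about 10 a year) qualifies. Under that rule the modelled inflation is small; the larger figures require mostly women below 8 cycles/year.
- *The misleading pattern is likely.* The chance that exactly one arm is significant, 2p(1 − p), can reach 50%, but the direction favouring acupuncture is half of that and cannot exceed 25%.
- *The baseline is distorted by memory or by contraceptive months.* Section 2.5.1 says only that the average is recorded. It must look back, but its source is not given. Oral contraceptives in the earlier part of that year could raise or lower frequency. The point needs neither.

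It is also fair to say that a within-arm 95% CI read against zero is the paired t-test in another form. The fix has to allow for that.

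**Conclusion.** The point holds as a problem of interpretation in supplementary analyses. The within-arm tests cannot show that acupuncture outperforms usual care, for menstrual frequency or for the continuous secondary outcomes. For menstrual frequency the bias may be slight (rejection of 4% to 9% under the stated entry rule) or substantial (6% to 43% if most entrants have fewer than 8 cycles/year). Which applies depends on cycle distributions and an entry mix that the article does not give. The 12% to 25% for a falsely favourable pattern further assumes equal change of 0.03 to 0.07/month and an SD of change of 0.17. The change is worth making because it costs almost nothing; the primary comparison is not at risk.

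**What to change.** In section 2.13, delete the within-arm significance tests for primary and secondary outcomes. Report within-arm mean change as description only, and say that it is not to be read against zero. Add a sentence stating that every efficacy statement rests on the baseline-adjusted between-arm ANCOVA difference and its 95% CI.

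The cost is one sentence removed and one or two added. The within-arm p-values are no longer reported. Data collection, patient numbers and sample size are unchanged.

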## Discussion

3

Acupuncture is widely practiced and has now been utilized in the Western countries as a treatment or adjunct treatment of an increasing number of conditions. It is a relatively safe treatment with few side effects.^[30]^ Acupuncture activates and modulates the nervous pathways at peripheral (local), segmental (in the spinal cord), and supraspinal levels within the central nervous system. The hypothetical mechanism of the effects of acupuncture in PCOS is that stimulation of acupuncture needles in the skeletal muscles excites ergoreceptors that activate afferent sensory nerve fibers. These signals are transmitted to the spinal cord, where they may modulate the sympathetic output to the target organs in the same area of innervation through spinal reflexes. Signals also reach the central nervous system via supraspinal pathways, and here they can exert central effects. Hypothalamic β-endorphin has been implicated in the effects of acupuncture. It modulates the autonomic system but may also alter the release of gonadotropin-releasing hormone and corticotropin-releasing hormone. These hormones exert an effect on reproductive function (via LH and FSH), adrenal function (adrenocorticotropic hormone), and pancreatic function (circulating β-endorphins).^[31]^

In a recent Cochrane review, true acupuncture did not show clinically relevant differences in the live birth rate, multiple pregnancy rate, ovulation rate, clinical pregnancy rate, or miscarriage rate when compared to sham acupuncture.^[19]^ Most previous RCTs examined the efficacy of acupuncture compared to sham acupuncture, but the appropriate control group in acupuncture trials is debatable. This is because non-penetrating or superficial acupuncture is not completely inert.^[32]^ According to a review of acupuncture trials, most studies found no statistically significant difference in the outcomes, and sham acupuncture could be as efficacious as true acupuncture, especially when superficial needling is applied to nonpoints. There is nothing sham about inserting needles into a patient, and it appears that researchers conducting acupuncture trials may be ignorant about how acupuncture works, or they may have employed a control treatment that cannot be scientifically distinguished from the intervention.^[33]^

Sham acupuncture is useful in RCTs in which subjective outcomes are affected by the success of blinding. In our trial, objective outcomes and menstrual frequency, which might be relatively less affected by whether blinding is performed or not, will be used. In the aforementioned Cochrane review, low-frequency electroacupuncture was more effective in restoring the regular menstrual period than physical exercise or no intervention was in PCOS patients, but the quality of the evidence was very low.^[19]^ Therefore, an RCT to examine the efficacy of acupuncture compared to that of physical exercise or no intervention is needed. In our study, we will use participants undergoing usual care (regular meals, sufficient sleep, and appropriate exercise) as the control group. Moreover, this is the first multi-country, multi-center RCT conducted for PCOS in Korea and China. The results of this study will provide evidence for guiding future clinical decisions and guideline development, as well as for a full-scale clinical trial.
